### Data collection

Recruitment of patients will be done by their doctor (a study researcher) during a primary care consultation, who will collect the data for the various variables by means of a personal interview and review of the computerized clinical record, after having obtained informed consent, and will record it in an electronic notebook for data collection (Figure 1).

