## Background

In 2010 the Spanish National Health System (NHS) paid for 958 million prescriptions according to data from a report by the Spanish Society of Public Health and Health Administration. Due to this massive exposure of the population to drugs, and to a non-negligible percentage of patients who suffer avoidable adverse effects, the risks associated with drug usage acquire an enormous relevance from the public health perspective [1].

In 2011–2012, legislative changes have been introduced in order to lower the pharmaceutical expenses in the NHS that affect drug prescription. The Spanish law Real Decreto-ley 9/2011, from August 19 [2], requires the medical prescription to be made according to active ingredient, official Spanish denomination, or common international denomination. This way, homogeneous groupings are established for the same active ingredient in order to facilitate the interchangeability of drugs. Later, the Real Decreto-ley 16/2012, from April 20, which addresses urgent measures to ensure the sustainability of the NHS [3], requires dispensing the lowest priced drug out of all the pharmaceutical bio-equivalent presentations, among other measures.

Since the entry of these laws into effect, the doctor writes the prescription according to the active ingredient, with some exceptions (therapeutic needs and lower cost), and the final choice for the commercial brand is determined by the pharmacy based on the lowest-cost criteria. Therefore, the pharmacy can make the necessary changes in order to adjust to the economic criteria.

In this new legal framework, the patient can receive multiple presentations of the same drug when periodically renewing a chronic treatment using the same active ingredient, with different shapes, colors, and sizes of pills, excipients, and packages.

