### Variables

The main outcome variable is a final combined variable, defined as “having made some drug usage error and/or an inadequate adherence to treatment regimen”.

Error in drug usage is defined according to the classification proposed by Ruiz-Jarabo *et al*. [18]. The type of error will be recorded (wrong dose, wrong frequency), as well as if there was injury to the patient, in which case the type and severity will also be recorded.

Inadequate adherence will be considered if more than one forgotten dose is detected during the package counting and/or if any of the answers (Yes/No) to the 4 questions of the Morisky-Green test in its validated Spanish version [19] is wrong. In the case of discrepancies between the Morisky test and the counting, the outcome of the counting will prevail. Since one single forgotten dose is a very stringent level of accomplishment, if no adherence differences are observed, different degrees of adherence (80%, 90% and 110%) will be considered.

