### Secondary outcome variables

#### Sociodemographic

Age, sex, level of education (illiterate, without studies, primary studies, secondary studies, superior education), and PHCC.

Related to the prescription and active ingredient:Prescribed active ingredient: enalapril, amlodipine, or simvastatin.Change of drug presentation at the pharmacy (Yes/No).Number of changes per drug.Suffering an adverse reaction to the drug (Yes/No), interruption of medication (Yes/No), and the reason for such interruption.Number of avoidable and non-avoidable adverse effects during the follow-up period.Tolerance of the patients to the dispensed drugs according to their own direct statement.

Clinical and analytical:Years of development of HTN and/or dyslipidemia. Presence of pathologies that modify the HTN (nephropathologies, sleep apnea, obesity, and malnutrition). Presence of pathologies that modify the lipid profile (hyperthyroidism, hypothyroidism, obesity, and malnutrition). Comorbidity (cardiovascular pathology, neurological pathology).Treatments that modify BP and the lipid profile (diuretics, alpha and beta blockers), anti-inflammatories, antidepressants and anxiolytics, thyroxin, hormone replacement therapy. Other concomitant treatments.Figures of systolic blood pressure (SBP) and diastolic blood pressure (DBP) in each visit. Difference of SBP and DBP between the first visit and the last recorded data. Percentage of patients with good control at the beginning and at the end of the study.Total HDL cholesterol, LDL cholesterol, and triglycerides, both initial and after one year.Initial and final weight. Initial height. Difference in body mass index (BMI) between the first and final visits.

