**Table 1 Tab1:** **Visits and procedures to be performed**

	***Visit*** **1** ***Screening*** **(0 months)**	***Visit 2*** **(3 months)**	***Visit 3*** **(6 months)**	***Visit 4*** **(9 months)**	***Visit 5*** **(12 months)**
Recruitment following the selection criteria	X				
Informed consent	X				
Initial collection clinical information and sociodemographic data	X				
BP control	X	X	X	X	X
Lipid profile control	X		X		X
Counting of drug packages		X	X	X	X
Morisky-Green test	X	X	X	X	X
Data collection for errors and adverse effects		X	X	X	X
Collection of followed-up clinical variables		X	X	X	X

If adverse effects are detected, the notification system for adverse reactions will be followed according to standard clinical practice.

In the case that one patient does not attend a visit, at least 3 attempts to contact them by phone will be performed during different days and hours. Patients lost to follow-up and abandonments will be recorded and the reasons noted.

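### The patient's own doctor records both the change of presentation and the usage errors, with no stated safeguard against asking harder where packs differ

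*Protocol article*

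**What the plan says.** All statements are in the protocol article.

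- **Who collects.** Data collection: "Recruitment of patients will be done by their doctor (a study researcher) during a primary care consultation, who will collect the data". The stated sources are an interview with the patient and the electronic record, with no split between exposure and outcome. The Discussion adds that patients are monitored throughout by their own primary care doctors.
- **Exposure.** Secondary outcome variables lists change of presentation at the pharmacy (yes/no) and the number of changes per drug. The Background explains that "the final choice for the commercial brand is determined by the pharmacy", so the doctor learns of a change only after dispensing.
- **Main outcome.** Variables defines it as "having made some drug usage error and/or an inadequate adherence to treatment regimen". One recorded error is enough to make a patient a case. On errors it says: "The type of error will be recorded (wrong dose, wrong frequency), as well as if there was injury to the patient". It cites a classification but does not say who applies it.
- **Adherence part.** It uses a package count and the four yes/no Morisky-Green questions. The count prevails if they disagree.
- **Timing.** Table 1 schedules "Data collection for errors and adverse effects" at visits 2 to 5, the same visits as the package count. It has no row for presentation changes.
- **Safeguards.** The Discussion describes training and a common notebook, both meant to reduce variability among professionals. The only independent role named (Sampling) is drawing the sample.

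**The concern.** The errors this study looks for, such as confusing packs or duplicating doses, are the ones that two different-looking packs bring to mind. A doctor who knows the hypothesis and has just handled two such packs has a prompt to ask further questions. The same doctor facing a patient with a single pack has none. If errors are elicited more fully in exposed patients, the error rate rises in that group with no true difference.

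This bias acts between exposed and unexposed patients of the same doctor. Reducing variability between doctors does not remove it, nor does adjusting for clustering or adding covariates to the logistic model. It cannot be repaired once the data are collected. The Aim names usage errors alongside adherence, so a distorted error comparison matters in itself as well as through the composite.

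**Working it through.** The plan states no figure on this point, so there is none to reproduce. The check has two parts.

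**1. Does the text separate exposure from outcome?** Data collection gives one person the variables in general, without splitting them. Table 1 places the error questions and the package count at the same visits. Neither Variables nor Data analysis names a second or masked assessor. Training has a different stated purpose. The text therefore provides no separation.

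**2. How large could the effect be with no true difference?**

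Inputs:
- True error rate e, equal in both groups: 10%, 20% or 30% (assumed).
- Detection probability s: 50-70% in unexposed and 80% in exposed patients (assumed).
- Non-adherence a = 50% in both groups: the complement of the 50% adherence in Sample size.
- Errors independent of adherence (assumed).

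Formulas:
- Observed error rate = e × s.
- Composite rate = 1 − (1 − a)(1 − e × s).
- Odds ratio (OR) = [p1/(1 − p1)] / [p0/(1 − p0)], with 1 = exposed and 0 = unexposed.

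| Case | e | s unexposed / exposed | Errors observed | OR, errors | Composite | OR, composite |
|---|---|---|---|---|---|---|
| Low | 10% | 70% / 80% | 7% vs 8% | 1.16 | 53.5% vs 54.0% | 1.02 |
| Central | 20% | 60% / 80% | 12% vs 16% | 1.40 | 56.0% vs 58.0% | 1.09 |
| High | 30% | 50% / 80% | 15% vs 24% | 1.79 | 57.5% vs 62.0% | 1.21 |

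Central case in full:
- Errors: (0.16/0.84)/(0.12/0.88) = 1.40.
- Composite: 1 − 0.5 × 0.88 = 0.56 and 1 − 0.5 × 0.84 = 0.58, so (0.58/0.42)/(0.56/0.44) = 1.09.

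**Sensitivity.** A wider grid was also run: error rate 5-30%, detection 50-60% in unexposed and 70-90% in exposed patients, non-adherence 50% or 30%. The composite OR ran from about 1.01 to 1.41 and the error-only OR reached 2.10. The top composite value needs 30% non-adherence, 30% errors and detection of 50% vs 90%.

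The chance of p < 0.05 with no true effect was approximated with an assumed 120 patients per group, a two-sided test and no clustering. It is 6.1% in the central case. With 30% errors and detection of 50% vs 90%, it is 15.8% at 50% non-adherence and 25.7% at 30%. If errors and non-adherence tend to occur in the same patients, the composite effect is smaller than shown.

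**The case against.** The strongest reply is that the damage to the main analysis is small. A reader might take 1.79, or the 2.10 from the wider grid, set it beside the OR of 2 in Sample size, and conclude that probing alone could produce the planned effect. The documents do not support that. The logistic model uses the composite, where the same assumptions give 1.02 to 1.21. This part of the reply stands in full.

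Three other stronger readings also fail:
- **The Morisky-Green result is equally at risk.** It consists of four fixed questions in a validated version, and the package count overrides it, so probing has less room to act.
- **Adverse effects are biased by exposure.** The plan lists "Number of avoidable and non-avoidable adverse effects during the follow-up period" as a secondary variable, and the Aim only estimates their frequency. They are outside the composite, and no comparison by exposure is stated for them.
- **The doctor demonstrably classifies errors unblinded, at the same interview as exposure is recorded.** The text never mentions blinding, does not say who applies the classification, gives no visit row for presentation changes, and also names the clinical record as a source. Awareness of exposure is an inference, though the natural one.

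It can also be said that question order and scripting belong in the notebook or a full protocol, neither of which is shown, and that harder probing is conjecture. Both are fair, and a script may already exist. What remains is the stated allocation of both measurements to one researcher-doctor, with the only stated safeguard aimed at something else.

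**Conclusion.** The point holds as a cheap improvement. It is not an error in a figure or a contradiction between sections. The plan gives exposure and usage errors to the same researcher-doctor, who on the natural reading knows the exposure, and counts packages at the visits where errors are elicited. Errors, which alone can trigger the main outcome, are therefore open to unequal elicitation.

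The illustrated bias is moderate for errors taken alone and small for the composite, about 1.09 in the central case. These sizes rest on assumed error and detection rates, on 50% non-adherence and on independence of errors and adherence. They show what is possible and do not estimate what will happen.

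**What to change.** 1. In the electronic notebook, ask every patient the same scripted set of error questions at visits 2 to 5. Save and lock the answers before the package count and before presentation changes are entered.
2. Flag any error found only during or after the count, and repeat the main analysis without those errors.
3. Name differential ascertainment of errors as a limitation in the Discussion, beside the lack of randomization. If the notebook already fixes the question order, say so.

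The cost is re-ordering and locking notebook pages, one extra analysis and slightly less flexible visits. The protection is partial: the count stays unblinded, and the doctor may remember a change from an earlier visit.

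Masked classification of errors at another centre is not recommended as the remedy. It adds assessors and does not cure unequal elicitation. Because the composite counts any error, re-reading the error type alone would not change it.

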**Figure 1 Fig1:**
[figure not shown]
**General scheme of the study.** Randomization and patient follow-up.

The study entails 5 visits during the trial period, set at 0, 3, 6, 9, and 12 months. Table 1 describes the visits scheme and the variables and measurements to be recorded during each one.

**Table 1 Tab1:** **Visits and procedures to be performed**

	***Visit*** **1** ***Screening*** **(0 months)**	***Visit 2*** **(3 months)**	***Visit 3*** **(6 months)**	***Visit 4*** **(9 months)**	***Visit 5*** **(12 months)**
Recruitment following the selection criteria	X				
Informed consent	X				
Initial collection clinical information and sociodemographic data	X				
BP control	X	X	X	X	X
Lipid profile control	X		X		X
Counting of drug packages		X	X	X	X
Morisky-Green test	X	X	X	X	X
Data collection for errors and adverse effects		X	X	X	X
Collection of followed-up clinical variables		X	X	X	X

If adverse effects are detected, the notification system for adverse reactions will be followed according to standard clinical practice.

In the case that one patient does not attend a visit, at least 3 attempts to contact them by phone will be performed during different days and hours. Patients lost to follow-up and abandonments will be recorded and the reasons noted.

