### Patients

All patients who are over 65 years old, diagnosed with HTN and/or hypercholesterolemia, and included in a program for following-up chronic patients in PHCCs will be included. The patient must be under treatment with at least one of the following drugs: enalapril, amlodipine, and simvastatin, with a stable dose during the previous 3 months, and must give informed, written consent.

The criteria for exclusion are: having difficulty to properly understand written or spoken Spanish, foreseeing an address change and not being ascribed to the PHCC for the following year, and suffering from severe systemic disease or other limitations that prevent the patient from attending the PHCC for the follow-up visits.

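### Table 1 schedules no package count at visit 1, so forgotten doses in months 0–3 cannot be derived accurately from the scheduled measurements

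*Protocol article*

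**What the plan says.** The article gives the timetable directly: "The study entails 5 visits during the trial period, set at 0, 3, 6, 9, and 12 months". It adds that "Table 1 describes the visits scheme and the variables and measurements to be recorded during each one". In Table 1 the row "Counting of drug packages" is marked at visits 2 to 5 only. Blood pressure and the Morisky-Green test are marked at all five visits.

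The Patients section requires treatment "with a stable dose during the previous 3 months".

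The Variables section defines the main outcome as "having made some drug usage error and/or an inadequate adherence to treatment regimen". For the adherence part: "Inadequate adherence will be considered if more than one forgotten dose is detected during the package counting", or if any Morisky-Green answer is wrong. The two sources are ranked: "In the case of discrepancies between the Morisky test and the counting, the outcome of the counting will prevail". A looser standard is held in reserve: "if no adherence differences are observed, different degrees of adherence (80%, 90% and 110%) will be considered".

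**The concern.** A package count measures what is left. To turn it into doses taken over an interval, one also needs what was there at the start and what was added. For the three later intervals the previous visit's count supplies the start. For months 0–3 nothing scheduled does, although patients already taking the drug will often have tablets at home.

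The adherence rule leaves little room for error: two missed doses in about 90 days are enough. The count outranks the questionnaire, so a correct Morisky-Green result does not rescue a patient whose count is wrong, and inadequate adherence alone makes the combined outcome positive. An error in opening stock therefore passes straight into the main outcome. Stock not recorded at entry cannot be recovered by any later analysis.

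**Working it through.** The plan states no figure on this point, so there is none to reproduce. The check is a stock balance followed by an illustration of consequences.

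**Balance for months 0–3.** Let S be tablets in hand at visit 1, D tablets dispensed up to visit 2, R tablets remaining at visit 2, and P tablets prescribed.

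- Doses taken = S + D − R
- Forgotten doses = P − (S + D − R)
- If S is left out, apparent forgotten doses = P − (D − R) = true forgotten doses + S

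The error equals S, and it always points towards non-adherence.

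**Assumed example:** one tablet a day, P = 90, D = 112, all 90 taken. Then R = S + 112 − 90 = S + 22, and apparent forgotten doses = 90 − (112 − S − 22) = S.

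| S | Apparent forgotten doses | Apparent adherence, (90 − S)/90 | Fails the main rule? |
|---|---|---|---|
| 0 | 0 | 100% | no |
| 1 | 1 | 98.9% | no |
| 2 | 2 | 97.8% | yes |
| 5 | 5 | 94.4% | yes |
| 14 | 14 | 84.4% | yes |
| 28 | 28 | 68.9% | yes |

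At the reserve levels, 14 leftover tablets pass at 80% but fail at 90%, and 28 fail both.

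**How often S could be 2 or more.** Pack size and stock at entry are not given. If S were uniform on 0 to N − 1 for a pack of N, P(S ≥ 2) = (N − 2)/N: 80% for N = 10, 90% for 20, and 93% for 28 or 30. This is the chance of holding such stock under that assumption. It becomes a misclassification rate only if opening stock is also ignored.

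**Possible effect on the comparison.** Suppose a share f of truly adherent patients ends up as cases in the final outcome, equally in both groups. Observed non-adherence is then p + f(1 − p), and the true difference is multiplied by (1 − f). I take 50% in the unexposed (from the planned 50% adherence) and, from the planned odds ratio of 2, 66.7% in the exposed. With 120 per group (the stated 240, equal split assumed) and a two-sided 0.05 test:

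| f | Difference (points) | Odds ratio | Power |
|---|---|---|---|
| 0 | 16.7 | 2.00 | 75% |
| 0.10 | 15.0 | 1.91 | 67% |
| 0.25 | 12.5 | 1.80 | 55% |
| 0.50 | 8.3 | 1.67 | 36% |

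Using the plan's 20-point difference instead (50% against 70%), power is 89%, 83%, 72% and 49%. The documents do not give f, so these rows show sensitivity and are not estimates.

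**With S counted at visit 1,** a fully adherent patient scores 0 forgotten doses whatever the leftover stock. No sample-size figure in the article changes.

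**The case against.** The strongest reply is that the article never says how a count becomes forgotten doses. It speaks of forgotten doses detected at the count and does not equate leftover tablets with them. Opening stock might be asked at the visit 1 interview, or avoided by counting only packs opened after entry, and a condensed article may leave such detail to the full protocol. This stands against any flat statement that the first interval is incalculable or that adherent patients are classed as non-adherent; both require opening stock to be ignored. It does not remove the gap. Counting only new packs needs the date the old one ran out, dispensing records show supply and not tablets at home, and an interview answer would have to be accurate to a single dose. None of these is a scheduled measurement, and the article presents Table 1 as the list of what is recorded at each visit.

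Three stronger readings are tempting, and the documents do not support them.

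- A reader might infer that one false failure makes a patient a case for the whole year. The article does not say how visit results are combined.
- A reader might infer that nothing softens the error. The 80%, 90% and 110% levels do so in part, but only if no adherence difference is seen first, so they do not protect the main definition.
- A reader might infer that the starting presentation also goes unrecorded. Table 1 has no row for presentation changes at any visit, yet they are listed among the variables, so absence from the table proves nothing there. The general data collection at visit 1 may well capture the drug in use.

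Dilution of the association also assumes equal error in exposed and unexposed patients, which is not established.

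**Conclusion.** The point holds in limited form. Followed as written, the schedule gives no measured opening stock for months 0–3, so forgotten doses in that interval cannot be derived accurately from the scheduled measurements. If opening stock is ignored, two or more tablets in hand at entry are enough to fail a fully adherent patient, and the count then overrides a good Morisky-Green result.

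One of four counting intervals is directly affected, because the month-3 count can open the next one. The effect on the one-year outcome depends on the unstated rule for combining visits. Its size is unknown: the 80–93% range rests on assumed pack sizes and uniform stock, and the power figures on an assumed f. This should be fixed, with moderate confidence, because the count is the deciding measure of adherence in the main outcome and the missing datum cannot be recovered later.

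**What to change.** Mark the package count at visit 1 in Table 1. Record tablets in hand for each study drug, using the fields already planned for visits 2 to 5, and calculate months 0–3 as opening stock plus dispensed minus remaining. The cost is small but not nil: visit 1 is the recruitment consultation, so patients must be asked beforehand to bring their packs, or the count must be done shortly after consent.

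Where no visit 1 count is available, use the month-3 count only as opening stock and base count adherence on months 3–12. This needs no new procedure and loses three months of count data. If it applies to only some patients, their count window is 9 months against 12 for the rest, so repeat the analysis on months 3–12 for everyone as a check.

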### Aim

The main aim of this study is to evaluate if changes of drugs with different package and/or presentation appearance for the same active ingredient are related to a decrease in adherence and an increase in usage errors, in patients ≥65 years old, undergoing chronic treatment with antihypertensives (enalapril and/or amlodipine) and hypolipidemic agents (simvastatin), over a one-year follow-up period.

The secondary objectives are: to describe the number of drug changes made at pharmacies, estimate the frequency of avoidable and non-avoidable adverse effects during the follow-up period, describe the tolerance of patients to the dispensed drugs, and study if the number of changes is related to a decrease in the degree of control of blood pressure (BP) and/or LDL cholesterol.

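### Usage errors are first recorded at month 3 in patients already on long-term treatment, so errors present at entry cannot be separated from new ones or adjusted for

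*Protocol article*

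**What the plan says.** The Aim asks whether changes of appearance "are related to a decrease in adherence and an increase in usage errors" over one year. The main outcome, under Variables, is "having made some drug usage error and/or an inadequate adherence to treatment regimen". It is not limited to errors that begin during follow-up.

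Table 1 sets out what is recorded at each visit:

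- "Data collection for errors and adverse effects": months 3, 6, 9 and 12, blank at visit 1.
- "Morisky-Green test": all five visits, including visit 1.
- "Counting of drug packages": months 3, 6, 9 and 12, blank at visit 1.

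Under Patients, those eligible must already be on a study drug "with a stable dose during the previous 3 months". The exclusions concern language, a foreseen change of address and inability to attend. None concerns usage errors already being made.

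Sample size frames the comparison as exposed versus non-exposed patients. Data analysis plans a logistic model of the combined yes/no outcome on variables found to be associated in bivariate analysis.

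**The concern.** The error types that the article names, wrong dose and wrong frequency, can be standing habits. Patients have been treated for at least three months before entry. According to the Background, the dispensing rules already allowed presentations to change. A habit that predates entry can first be found at month 3, and it then makes the patient a case whether or not any presentation changed during the study.

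Two things are at stake. If standing errors are equally common in both groups, they add the same background to each and pull the odds ratio towards 1. If they are not, they confound the association, and the Discussion acknowledges that exposure cannot be randomised. Entry error status is the most direct variable to adjust for, and it is the one not recorded.

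**Working it through.** **Schedule.** Errors have their own row in Table 1, and it is blank at visit 1 while the Morisky-Green row is marked there. The blank is thus a stated schedule, not a detail left to a fuller document. The Morisky-Green test does not fill the gap, because the Variables section uses it for adherence and classifies errors separately.

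**Inputs.** The article gives no figure for errors at entry, so there is none to reproduce.

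- From Sample size: 50% adherence, hence 50% inadequate adherence, and OR = 2. I apply these to the combined outcome. Odds of 1 × 2 = 2 give 2/3 = 66.7% in the exposed.
- Assumed: a share h with a standing error at entry that persists and is detected, independent of other events; h = 5%, 10%, 20%.
- Assumed for errors alone: new-error risks of 20% v 33.3%, or 10% v 18.2%. Both are OR 2.

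**Formula.** With new-event risks a (non-exposed) and b (exposed): A = h + (1 − h)a, B = h + (1 − h)b, observed OR = [B/(1 − B)] / [A/(1 − A)].

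**Equal standing errors (dilution).** Worked case, main outcome, h = 0.20: A = 0.20 + 0.80 × 0.50 = 0.600; B = 0.20 + 0.80 × 0.667 = 0.733; OR = 2.75/1.50 = 1.83.

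| h | Main outcome, 50% v 66.7% | Errors alone, 20% v 33.3% | Errors alone, 10% v 18.2% |
|---|---|---|---|
| 0 | 2.00 | 2.00 | 2.00 |
| 5% | 1.95 | 1.83 | 1.69 |
| 10% | 1.91 | 1.71 | 1.53 |
| 20% | 1.83 | 1.56 | 1.36 |

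For errors at 20% v 33.3%, standing errors make up h/A of the non-exposed error cases: 0.05/0.24 = 21%, 0.10/0.28 = 36%, 0.20/0.36 = 56%.

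For the main outcome with 120 patients per group (half of the planned 240, equal groups assumed, two-sided 0.05, normal approximation, clustering ignored), power goes from 0.75 at h = 0 to 0.71, 0.67 and 0.59.

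**Unequal standing errors (confounding).** Suppose there is no true effect, with a = b = 0.50.

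- h = 10% in the non-exposed and 20% in the exposed: A = 0.55, B = 0.60, OR = 1.500/1.222 = 1.23.
- h = 10% and 30%: A = 0.55, B = 0.65, OR = 1.857/1.222 = 1.52.
- Groups reversed (30% and 10%): OR = 1/1.52 = 0.66.

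The bias can go either way, and the planned data cannot show which.

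**The case against.** The strongest reply is that the Aim asks about a relation and that the analysis compares exposed with non-exposed patients. No within-patient change is planned. A standing error is background risk, which the non-exposed group is there to measure. This stands: a reader might infer that no increase in errors can be shown at all, and the article does not support that. An excess in the exposed can be estimated without an entry value.

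Three further points also have weight.

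- **Size.** The larger reductions belong to the error component, not to the combined outcome, where the dilution is milder. If standing errors cluster in non-adherent patients, it is milder still. The assumed range may also be too high. The only error frequency in the Background is about 1.01%, from a study of primary care consultations. It measures something else and does not settle the share, but at h = 1% the odds ratios would be 1.99 (main outcome) and 1.96 (errors, 20% v 33.3%).
- **Adjustment.** It would be wrong to say that nothing collected helps. Age, education, neurological disease, other comorbidity, concomitant treatment and the visit 1 Morisky-Green result are plausible markers of error-prone patients. They are proxies, however, and enter the model only if associated in bivariate analysis.
- **Remedy.** Restricting the outcome to new errors would leave the adherence component unrestricted. The package count, which prevails over the questionnaire, has no visit 1 value either. Entry errors may also result from earlier changes of presentation, so conditioning on them could remove part of the effect of interest.

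These points limit the claim and shape the fix. They do not remove the gap: errors at entry and new errors remain indistinguishable, and exposure is not randomised.

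**Conclusion.** The point holds in a limited form. With errors first recorded at month 3 in patients already under treatment, and an outcome that counts any error, entry errors cannot be told from new ones, a within-patient increase cannot be shown, and entry error status cannot be adjusted for directly.

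Under equal standing errors of 5% to 20%, the effect on the main outcome is modest: an odds ratio of 2 becomes 1.95 to 1.83. For errors alone it is larger, 1.83 to 1.56 at 20% v 33.3%. Confounding is the less predictable risk: with no true effect, 10% v 30% standing errors produce an odds ratio of 1.52 or 0.66, depending on which group carries more. All of this rests on assumed shares and, for errors alone, on assumed risks. The figures show scale and are not predictions.

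**What to change.** 1. In Table 1, mark the usage-error item at visit 1, with the same classification as at later visits.
2. In Data analysis, enter visit 1 error status and the visit 1 Morisky-Green result as fixed covariates in the logistic model, whatever the bivariate results.
3. Keep the main outcome as defined, and report errors new since visit 1 as a sensitivity analysis.
4. If no visit 1 record is taken, word the Aim as a between-group difference in error frequency and not as an increase.

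The cost is a few minutes at a visit where the doctor already interviews the patient and reviews the record, plus a line in the table and a sentence or two in the analysis. There are two downsides to state. Asking about errors at visit 1 may prompt their correction, and so alter what is later observed. Adjustment may also absorb some effect of changes made before entry. The missing visit 1 package count is a parallel gap that this change does not close.
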